## Abstract

**Background:**

Adoption of sustainable menstrual products, such as menstrual cups (MCs) and menstrual panties (MPs), remains low in India despite national menstrual hygiene initiatives. Cultural taboos, low awareness, and misinformation are significant barriers. This study develops and evaluates a community-based intervention led by trained community health workers and female teachers to promote sustainable menstrual product use among adolescent girls.

**Objective:**

This study aimed to (1) assess the impact of sensitization and training on the knowledge, attitudes, and practices of community health and education workers; (2) evaluate the effectiveness of their community campaigns in improving girls’ awareness and readiness to adopt MCs and MPs; (3) examine the acceptability and user experience of MCs and MPs over 12 months; and (4) conduct an economic evaluation of MCs and MPs.

**Methods:**

This is a mixed methods, 2-phase interventional feasibility study at 2 Indian sites (Kalyani, West Bengal, and Chandigarh and Panchkula, North India), chosen to represent contrasting urban-planned and mixed urban-rural catchments. Phase 1 trains 40 community health and education workers (accredited social health activists, auxiliary nurse midwives, Anganwadi workers, and female teachers), who then deliver structured education to 912 adolescent girls in phase 2. A subset of 406 girls will be allocated to MCs or MPs and followed for 12 months via diaries, home visits, and focus group discussions. Quantitative data will be analyzed in SPSS; qualitative data will undergo reflexive thematic analysis in NVivo, guided by the Behavior Change Wheel and Capability, Opportunity, Motivation–Behavior framework. A cost-utility analysis using EQ-5D-Y and quality-adjusted life-years will assess cost-effectiveness from a societal perspective.

**Results:**

The study is funded by the Indian Council of Medical Research (proposal IIRPSG-2024-01-03552), with funding confirmed in March 2024. Ethics approval was obtained in January 2024 (Postgraduate Institute of Medical Education and Research, Chandigarh) and in April 2024 (All India Institute of Medical Sciences, Kalyani). Phase 1 sensitization was completed at both sites by September 2024, with all 40 workers trained (retention 100%). As of March 2026, 512 of 912 (56%) adolescent girls have completed phase 2 sensitization, and 210 of 406 (52%) have been enrolled and allocated to MCs or MPs in phase 3. Data collection is expected to conclude by December 2026, with analysis in early 2027 and outcome findings to be submitted for publication by late 2027.

**Conclusions:**

This feasibility study will generate evidence on the acceptability, usability, and cost-effectiveness of a community worker– and teacher-led model for promoting sustainable menstrual products among adolescent girls, informing scale-up strategies in similar low- and middle-income settings.

## Introduction

### Background

Menstrual hygiene management remains a critical health and equity concern for adolescent girls in India and other low- and middle-income countries. Although national schemes such as the Menstrual Hygiene Scheme and the Rashtriya Kishor Swasthya Karyakram have improved access to disposable sanitary pads, sustainable alternatives such as menstrual cups (MCs) and menstrual panties (MPs) have yet to gain significant traction [1,2]. According to National Family Health Survey–5 data, only 64% of adolescent girls aged 15‐19 years in India use hygienic menstrual protection, and reusable options are rarely adopted [2]. Of the approximately 1.42 billion people living in India today, 22.2% of women are in their reproductive years; these women use sanitary pads, tampons, MCs, and cloths during menstruation, and on average a woman generates around 150 kilograms of nonbiodegradable menstrual waste over her reproductive lifespan, with conventional sanitary pads taking 500‐800 years to decompose [3-6].

MCs and MPs are regarded as more economical and eco-friendly alternatives to conventional products [1]. MCs have a lifespan of up to 10 years, while MPs provide reusable absorbent underwear that lowers monthly expenses and avoids internal insertion, making both options particularly suitable for low-resource settings [3,7]. Despite these benefits, uptake of MCs and MPs in India remains below 5% in most published reports, reflecting deeply rooted menstrual taboos, ignorance, virginity-related fears, and misconceptions regarding usability and safety [1,8-10]. More recent single-site studies continue to document this gap: cross-sectional surveys among young women in South India in 2024‐2025 report that although a majority have heard of MCs, actual awareness of correct use and uptake remain poor, with unfavorable attitudes documented in over half of respondents [6,11].

Evidence from other settings indicates that adolescent girls are more receptive to sustainable products when interventions combine peer support, structured education, and trusted facilitator involvement [1,11,12]. When MCs and MPs are introduced with supervision and peer support, they are more often perceived as discreet, comfortable, and acceptable [1,13-16]. Nonetheless, a critical gap persists in large-scale, community-based interventions that jointly address awareness generation and product distribution, particularly in the Indian context. Community health workers—accredited social health activists (ASHAs), auxiliary nurse midwives (ANMs), and Anganwadi workers (AWWs)—together with female schoolteachers, are well positioned to promote behavioral change among adolescent girls because of their existing community trust and reach. Their involvement is critical for shifting narratives, offering accurate guidance, and normalizing the use of reusable menstrual products [9]. In this manuscript, we use the term “community health and education workers” (rather than the broader term “stakeholders”) to refer specifically to this frontline group of ASHAs, ANMs, AWWs, and female schoolteachers of grades 8‐12, who are the direct recipients of phase 1 training and the subsequent deliverers of phase 2 community education; the term “stakeholders” is reserved for this same group throughout the manuscript for consistency and is not intended to include policymakers or other actors not directly involved in intervention delivery.

A recent qualitative analysis of Indian adolescent girls’ perspectives on menstrual health promotion found that girls consistently identified trusted adult facilitators, peer discussion, and early, repeated exposure to accurate information as key enablers of healthier menstrual practices, reinforcing the rationale for a facilitator-led model such as the one proposed here [17]. Similarly, a narrative review of menstrual health interventions for adolescent girls in rural India highlighted that decentralized, community-driven models—particularly those embedded within existing government frontline worker cadres—tend to be more sustainable than vertically delivered, one-off campaigns [9].

As this intervention seeks to change health behavior at both the facilitator and adolescent levels, its design is informed by the Behavior Change Wheel and its central Capability, Opportunity, Motivation–Behavior (COM-B) model, which conceptualizes behavior as a function of capability, opportunity, and motivation [18]. Capability is targeted through structured knowledge- and skills-based training (menstrual physiology, product use, and troubleshooting); opportunity is addressed by ensuring physical access to free products, demonstration materials, and socially supportive group settings (eg, single-sex workshops and guardian engagement); and motivation is targeted through myth-busting, testimonial-based messaging, and peer modeling delivered by trusted community figures. This framework guided both the content of the phase 1 training curriculum and the phase 2 adolescent sensitization modules and will subsequently guide the interpretation of qualitative findings on barriers and facilitators to adoption.

The current study addresses this implementation and knowledge gap by developing and evaluating a community-based, facilitator-led intervention to promote MCs and MPs among adolescent girls, through the sensitization and training of community health and education workers. Through workshops, campaigns, and peer engagement, these facilitators will disseminate knowledge and foster positive attitudes toward sustainable products. The novelty of the study lies in the simultaneous evaluation of both products, integrating educational outreach with a cost-utility framework within a single feasibility study. Findings are expected to inform culturally sensitive scale-up strategies across similar low- and middle-income countries contexts. This protocol outlines a 2-phase interventional feasibility study to investigate the feasibility, acceptability, and scalability of this community-driven model in 2 Indian settings.

### Objectives

This study aims to evaluate the feasibility, acceptability, and effectiveness of a community-based model for promoting sustainable menstrual products—MCs and MPs—among adolescent girls in 2 urban and mixed urban-rural Indian settings.

The specific objectives are as follows:

To assess the impact of sensitization and training of community health and education workers on their knowledge, attitudes, and practices regarding sustainable menstrual hygiene productsTo evaluate the effectiveness of facilitator-led community campaigns in enhancing adolescent girls’ awareness, knowledge, and readiness to adopt MCs and MPsTo examine the acceptability, challenges, and user experiences of adolescent girls using MCs and MPs over a defined 12-month periodTo perform an economic evaluation of MCs and MPs in terms of cost-effectiveness, sustainability, and affordability

## Methods

### Study Design

This study is designed as a 2-phase, interventional feasibility study using a mixed methods, convergent-parallel approach, in which quantitative and qualitative data are collected concurrently in each phase and integrated at the interpretation stage [19]. Phase 1 focuses on sensitization and preintervention assessment of community health and education workers, while phase 2 evaluates the effectiveness and acceptability of MCs and MPs among adolescent girls through direct intervention and structured follow-up. As a feasibility study, the protocol has been developed with reference to the CONSORT (Consolidated Standards of Reporting Trials) 2010 extension for pilot and feasibility trials and relevant SPIRIT (Standard Protocol Items: Recommendations for Interventional Trials) guidance for reporting trial protocols, adapted for a mixed methods, nonrandomized community intervention design [20,21].

### Study Setting and Rationale for Site Selection

The study will take place in 2 Indian sites, chosen to capture contrasting geographic and sociocultural contexts while retaining the feasibility of implementation within the study team’s existing institutional and field infrastructure (Figure 1):

Center 1—East India (Kalyani, West Bengal): Kalyani is a planned urban township in the Nadia district of West Bengal, approximately 50 kilometers (31 miles) from Kolkata. It functions as both a municipality and a community development block, and includes surrounding semiurban and rural catchment areas served by the affiliated primary health centers, allowing the capture of both urban and semirural adolescent populations within a single site.Center 2—North India (Chandigarh and Panchkula): Chandigarh is a union territory serving as the joint capital of Haryana and Punjab, recognized for its planned urban infrastructure. The study will include defined urban service areas of Chandigarh (Indira Colony and Sectors 25, 49, 50, and 52), together with Panchkula district, Haryana, which includes peri-urban and rural blocks, to allow comparison of urban and rural uptake within the same site.

The 2 sites were selected, in preference to a larger number of sites, to allow intensive, high-fidelity delivery of the facilitator-training and adolescent-sensitization components within the resources available for a feasibility study, while still enabling comparison across an eastern, planned-urban context (Kalyani) and a northern, mixed urban-rural context (Chandigarh-Panchkula). Recruitment at each site is organized at the level of predefined clusters (schools and their linked Anganwadi and health subcenter catchments), reflecting the fact that stakeholders and adolescent girls are naturally grouped within schools and community health worker catchment areas rather than sampled as unrelated individuals; this clustering was accounted for in the sample size calculation (see below) via a design effect. This represents a refinement of the original grant proposal, in which site selection was described in less detail; following external review of the funded proposal, the protocol was revised to make the cluster structure explicit and to ensure that both urban and rural and peri-urban catchments are represented at each site, rather than urban areas only, in order to improve generalizability of findings across the rural-urban gradient.

**Figure 1. F1:**
[figure not shown]
Map of India showing the 2 study centers.

### Study Participants

The study involves two key participant groups: (1) adolescent girls aged 13‐19 years (N=912) who were enrolled in schools or attended community centers and (2) community health and education workers (n=40; ASHAs, ANMs, AWWs, and female schoolteachers of grades 8‐12; Textbox 1).

Textbox 1.Eligibility criteria.
**Inclusion criteria**
Community health and education workersAll auxiliary nurse midwives (ANMs), accredited social health activists (ASHAs), and Anganwadi workers (AWWs) working in the selected health centersAll female schoolteachers involved in teaching grades 8 to 12AdolescentsAdolescent girls within the age group of 13‐19 yearsAdolescent girls who have attained menarcheResident of the city for the last 6 monthsAble to read and understand the local language or Hindi
**Exclusion criteria**
Community health and education workersMale schoolteachersANMs, ASHAs, AWWs, and teachers not providing consentAdolescentsGirls with disabilities or mental illness that would preclude participation in group sessions or self-administered questionnairesPregnant or lactatingNot providing assent or informed consent

### Study Flow and Sample Size Calculation

Figure 2 depicts the overall participant flow across all 3 phases of the study, from eligibility assessment and enrollment of community health and education workers in phase 1, through adolescent sensitization in phase 2, to product allocation and 12-month follow-up in phase 3. The figure has been drawn as a single, simplified linear flow to reflect the status as of March 2026 (see Results). Boxes shaded gray denote eligibility and target populations at each phase; boxes shaded blue denote participants actually enrolled and retained; and the green and orange boxes in phase 3 denote the MC and MP allocation arms, respectively.

For the adolescent cohort, assuming a baseline sustainable-product usage rate of 5% and a projected postintervention uptake of 20%, with 80% power and 5% significance, the minimum required sample size was calculated as 304 adolescent girls per site using a standard formula for comparing 2-proportions formula. To account for clustering by school and community catchment, a design effect of 1.5 (based on an assumed intracluster correlation coefficient of 0.02 and an average cluster size of 25 girls, consistent with design effects reported in comparable school-based menstrual health cluster studies) was applied, giving a minimum requirement of 456 adolescent girls per site (total N=912) for the phase 2 sensitization cohort. Of these, a subgroup of 416 girls (n=208 per site) will be enrolled in the phase 3 product-use follow-up; this subgroup size was determined pragmatically in line with recommendations for feasibility and pilot studies, which emphasize that a fully powered comparative sample is not required at this stage but that sample size should still be justified in relation to the primary feasibility objectives (recruitment, retention, and product continuation) rather than a hypothesis-testing end point [22,23]. A minimum of 30‐35 participants per arm per site is considered adequate to estimate continuation and acceptability proportions with reasonable precision (95% CI width ≤±16%) for feasibility purposes, and the planned 203 girls per site substantially exceeds this threshold, allowing additional precision for the secondary comparison between MC and MP users. Twenty community health and education workers per site will be enrolled (total n=40) for training and postintervention assessment; this number reflects the total eligible cadre of ASHAs, ANMs, AWWs, and grade 8‐12 female teachers attached to the selected clusters at each site, and was not derived from a formal power calculation, consistent with standard practice for facilitator and trainer cohorts in implementation feasibility studies.

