### Phase 2: Adolescent Sensitization and Recruitment

The sensitization intervention will be conducted in small-group workshops (approximately 20‐25 girls per group) using materials developed and validated in phase 1, covering menstrual health, hygiene, and correct usage of MCs and MPs. Sessions will be led by previously trained community health and education workers (ASHA, ANM, AWW, and female teachers), ensuring cultural sensitivity and local relevance, and will run for approximately 90 minutes across 2 sessions per group. Adolescents will be recruited as per the inclusion criteria above through school registers (for school-going girls) and community health worker household lists (for out-of-school girls), with information sessions held for parents and guardians prior to enrollment. Preintervention and postintervention questionnaires (structured, self-administered, in the local language) will measure changes in knowledge, attitudes, and perceived readiness to adopt MC and MP, using the same core knowledge and attitude domains as the phase 1 instrument, adapted to the adolescent literacy level. Additionally, 2 focus group discussions (FGDs) will be held at each site—one with adolescent girls and one with their female guardians—to explore barriers and facilitators to product adoption, using a semistructured topic guide based on the COM-B framework (Multimedia Appendix 2). Quantitative data will be analyzed using SPSS (version 26; IBM Corp), and qualitative data will undergo thematic analysis to develop a comprehensive understanding of the social and behavioral influences on sustainable menstrual product adoption.

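### The stated minimum of 304 girls per site does not follow from its own inputs, which give 76 per group (152 for two groups), and the quantity powered is not described as a phase 2 outcome

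*Protocol article*

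**What the plan says.** In the section Study Flow and Sample Size Calculation, the adolescent cohort is sized "assuming a baseline sustainable-product usage rate of 5% and a projected postintervention uptake of 20%, with 80% power and 5% significance". The method is given as "using a standard formula for comparing 2-proportions formula", and the result is that "the minimum required sample size was calculated as 304 adolescent girls per site".

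Clustering is then allowed for with "a design effect of 1.5 (based on an assumed intracluster correlation coefficient of 0.02 and an average cluster size of 25 girls". This gives 456 girls per site and 912 in total, presented as the minimum for the phase 2 cohort. The phase 3 subgroup is sized separately and pragmatically.

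Phase 2 has no control group. Girls complete questionnaires before and after the sessions, and these "will measure changes in knowledge, attitudes, and perceived readiness to adopt MC and MP" (Phase 2: Adolescent Sensitization and Recruitment). Table 1 assigns product use and continuation to the phase 3 diaries and home visits, and the outcome list in Phase 3: Intervention and Follow-up does the same.

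**The concern.** The paragraph gives its inputs, formula and answer, so it can be checked directly, and a difference of 15 percentage points should not need 304 girls per site. The figure feeds straight into 456 and 912, the headline sample size. As of March 2026, 512 girls had been sensitized, so 400 remain to be recruited toward a target described as a minimum requirement.

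Two further mismatches lie in the same paragraph. The standard two-proportion formula is for independent groups, whereas phase 2 compares the same girls before and after. And the proportion that is powered is product use, which the phase 2 section does not list among what its questionnaires measure.

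**Working it through.** **Inputs** (Study Flow and Sample Size Calculation): p1 = 0.05, p2 = 0.20, difference d = 0.15, power 80% (z = 0.8416), significance 5%. Sidedness is not stated; two-sided is assumed (z = 1.9600).

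**The plan's own later steps.** Design effect: 1 + (25 − 1) × 0.02 = 1.48, rounded to 1.5. Then 304 × 1.5 = 456 and 456 × 2 = 912. These steps are consistent (1.48 would give 450). The problem is the 304.

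**Two-proportion formula, pooled variance.** With p̄ = 0.125:

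n per group = [1.9600 × √(2 × 0.125 × 0.875) + 0.8416 × √(0.05 × 0.95 + 0.20 × 0.80)]² / 0.15²

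= [1.9600 × 0.4677 + 0.8416 × 0.4555]² / 0.0225 = 1.3001² / 0.0225 = 75.1, so 76.

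**Variants at 80% power and 5% significance:**

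| Variant | Per group | Two groups | Two groups × two sites |
|---|---|---|---|
| Two-sided, pooled | 76 | 152 | 304 |
| Two-sided, unpooled | 73 | 146 | 292 |
| Two-sided, simple pooled | 77 | 154 | 308 |
| Two-sided, continuity-corrected | 88 | 176 | 352 |
| Arcsine | 70 | 140 | 280 |
| One-sided, pooled | 60 | 120 | 240 |
| One-sided, continuity-corrected | 72 | 144 | 288 |

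None gives 304 per group or 304 for two groups at one site. The number appears only as 76 × 2 groups × 2 sites. Reaching about 304 for two groups at one site needs inputs the article does not state, such as 50% loss (152 / 0.5 = 304), or two-sided 1% significance with 90% power and continuity correction (312).

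**With the stated design effect:** 152 × 1.5 = 228 per site counting two groups, against 456 stated, a factor of two.

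**Power of the stated numbers for 5% against 20%,** from z = [0.15 × √n − 1.9600 × 0.4677] / 0.4555:

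- 304 split as 152 per group: z = 2.05, power 98.0%.
- 304 per time point: z = 3.73, power above 99.9%.

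**Paired version.** McNemar: n = [1.9600 × √ψ + 0.8416 × √(ψ − d²)]² / d², where ψ is the share of girls who change status. If the share who stop using is assumed to be 0 to 0.05, ψ runs from 0.15 to 0.25 and n from 50 to 85 girls per site (75 to 128 after × 1.5). When before and after are uncorrelated (0.05 × 0.80 = 0.04 stop), n is 78, close to 76. Pairing therefore does not explain 304.

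**What 456 per site delivers.** Effective number 456 / 1.5 = 304 per time point. Treating time points as independent, 80% power is reached for a rise from 5% to about 11.2%.

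**The case against.** The strongest reply is that the error is on the safe side. The calculation asks for more girls than needed, power for 5% against 20% is not threatened, phase 3 does not rest on this figure, and this is a feasibility study. That stands, and it limits the consequence to an unsupported justification. It does not make the derivation correct, and the exemption from a fully powered sample is stated only for the phase 3 subgroup; 912 rests on the power claim.

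It is also fair that pairing changes the number little, that the article does not describe its formula as unpaired, and that the choice of paired test can be left to an analysis plan.

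On the endpoint, the Data Analysis section mentions practice scores before and after and a regression on product adoption, and the adolescent questionnaire is in an appendix not shown. A usage item may therefore exist. What can be said is that the article describes no usage proportion across the 912 girls as an outcome.

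Two stronger readings are tempting and not supported:

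- A reader might infer that the study cannot show whether the campaign worked. Objective 2 concerns awareness, knowledge and readiness, and the phase 2 questionnaires cover knowledge and readiness before and after. A faulty sample-size paragraph does not stop that analysis.
- A reader might infer that uptake is settled by product supply, since 416 / 912 = 46% exceeds 20%. But 416 is a recruitment target that depends on consent or assent to use a product, and receiving a product is not using it. Likewise, the 210 girls allocated so far come from 512 sensitized, not from 912.

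**Conclusion.** The point holds as an error of derivation. From the stated inputs the requirement is 76 per group, 152 for two groups, and 228 per site with the design effect of 1.5; the article states 304 and 456. The stated minimum is twice what the inputs support when two groups are counted. This assumes a two-sided test and equal groups; other standard variants range from 60 to 88 per group, and none rescues 304 per site. That a two-site total was labelled as per site and doubled again fits exactly but is an inference.

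The study is not underpowered for 5% against 20%. What is unsupported is 912 as a minimum at 80% power, and the link between the powered quantity and an outcome described for the phase 2 cohort. The detectable rise to about 11% assumes independent time points and a design effect of 1.5 at each. A paired calculation on the same girls and clusters would differ, so that figure is a guide only.

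**What to change.** Rewrite the paragraph in one of two ways. Either correct the calculation (76 per group, 152 for two groups, 228 per site after the design effect), or state the inputs that produce 304, such as an allowance for loss or a different power or significance level.

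The total of 912 can be kept. In that case, state what 456 per site delivers, as power or as the smallest detectable change, for a paired comparison of a proportion measured before and after in phase 2. Readiness to adopt is the natural candidate. The 5% and 20% are usage rates and do not carry over to it, so the assumed readiness proportions and the share of girls expected to change should be given. If the phase 2 questionnaire already yields a usage proportion at both time points, name it as an outcome and power that.

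Adding a usage item to the post-session questionnaire alone would not solve this: it would have no matching baseline, and 512 girls have already been sensitized.

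The cost is one paragraph of text and a short recalculation. No additional girls are needed.
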